## Acupuncture group

4

Participants in acupuncture group will receive therapy at the Lianquan (RN23), Renying (ST9), Danzhong (RN17), Guanyuan (RN4), Qihai (RN6), Zusanli (ST36), Sanyinjiao (SP6) and Zhaohai (KI6) points. The acupuncture points are identified according to the method of point location issued by the WHO. After local area disinfection with alcohol wipes, RN4, RN6, ST36, KI6 and SP6 will be inserted perpendicularly 10 to 15 mm deep with a 0.25 mm × 40 mm acupuncture needle. RN17 (with the needle tip pointing towards the head) will be punctured obliquely 5 to 10 mm deep with a 0.25 mm × 25 mm acupuncture needle, while RN23 (with the needle tip pointing towards the root of tongue) will be punctured obliquely to the depth of 5 mm. ST9 will be punctured perpendicularly to a depth of 5 mm. De qi sensation (a compositional sensation including numbness, soreness, distention, heaviness) will be achieved through lifting, thrusting, and rotating.

## Sham acupuncture group

5

Participants in the control group will undergo treatment with a special sham acupuncture device with a blunt-tip needle (customize from Suzhou Huatu Medical Devices Co. Ltd.) which is similar to Streitberger needles device, without insertion.^[59]^ This non-invasive placebo needles can provoke a needling sensation as soon as it touches the skin. The acupoint selection and procedures will be the same as in the acupuncture group. The acupuncturists should pretend to manipulate the needle for 10 seconds on each point as well. No deqi sensation will be induced.

## Outcome measures

6

### Primary outcome

6.1

The primary outcome in this trial is the titers of TPOAb and TGAb at baseline and at the 4th, 8th, and 12th week after randomization.

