### Design

2.1

A single-center, patient-blinded, randomized controlled trial (RCT) is currently being performed. Acupuncture will be compared with sham acupuncture to determine if acupuncture has an effect on the reduction of antibody (TPOAb or TGAb) and fertility improving. The trial will be conducted in the Department of gynecology, Teaching Hospital of Chengdu University of Traditional Chinese Medicine. The protocol will be reported following the Consolidated Standards of Reporting Trials (CONSORT) statement and the Revised Standards for Reporting Interventions in Clinical Trials of Acupuncture (STRICTA).^[56,57]^ The flowchart of the trial is shown in Figure 1. The study schedule is detailed in Table 1. The Standard Protocol Items: Recommendations for Interventional Trials (SPIRIT) checklist is provided as Additional File 1.

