### Sample size

2.6

Sample size will be decided by the primary outcome. The primary outcome of this study will be the mean change of TPOAb and TGAb from baseline to week 12. According to the results of our previous pilot study, titers of TPOAb was 253.86 ± 178.23 IU/ml in the acupuncture group and 318.98 ± 201.37IU/ml in the sham acupuncture group (TPOAb higher than 34IU/ml was the positive threshold of this research center). Considering participants recruited in the two groups are in a 1:1 ratio, the following formula was used to estimate sample size: 
[figure not shown]

With a 5% significance level (*α* = 0.05, two-sided) and 80% power (*β* = 0.2), at least 134 patients should be enrolled in each group and 284 total participants will be recruited to allow for a 10% dropout rate.

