### Statistical analysis

6.5

Statistical analyses of data will be performed using SPSS21.0 software (International Business Machines Corp., Armonk, NY) by professionals who will be blinded to the whole trial process. According to the principle of intention-to-treat (ITT), all randomized participants will be analyzed. Continuous variables with normal distribution will be expressed as Mean ± Standard Deviation (M ± SD) and compared by an independent sample Student *t* test. For abnormally distributed variables, they will be expressed as Medians ± Interquartile Range (MIQR) and nonparametric tests will be used. Categorical variables will be presented by frequency and percentage and analyzed by χ^2^ test or Fisher exact test. A repeated-measures multifactorial analysis will be used to analyze value changes of TPOAb, TGAb, fT3, fT4, TSH, thyroxine, AMH, FSH, LH, and E2 across 4 testing time points (See Table 1). The rest of the secondary outcomes will compare the proportions of patients with primary ovarian insufficiency and different pregnancy outcome. Safety analyses will be compared with the incidence of AEs in two groups using the χ^2^ test. Missing data will be handled by multiple imputation methods. All the tests will be two-sided, and a *P* value of less than .05 will be considered statistically significant.

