Thyroid peroxidase (TPO) and thyroglobulin(TG) are involved in thyroid autoimmunity as important antigens.^[65]^ TPO is the key enzyme in thyroid hormone synthesis.^[66]^ The thyroid hormones T3 and T4 are synthesized in the thyroid gland in a process that crucially involves the iodoglycoprotein thyroglobulin (TG).^[67]^ Antibodies against the main thyroid antigens (such as TPOAb and TGAb) can induce a chronic lymphocytic thyroiditis, eventually leading to the destruction and loss of thyroid function.^[21,68]^ TGAb may reflect a more initial type of immune response, while TPOAb can characterize later adaptive immune response, a sort of immune escalation. Positive TPOAb and/or positive TGAb, have been used test for screening for HT.^[69]^ TPOAb (positive in 95% of HT patients) as the best serological marker of HT is more sensitive than TGAb (positive in only 60%–80% of HT patients).^[7,70]^ Some surveys suggest that positive TPOAb are associated with an increased risk of developing hypothyroidism.^[11,12]^ In a cohort study, a TPOAb level above the threshold of 500 IU/ml was associated with a moderately increased risk for developing hypothyroidism.^[11]^ The presence of TPOAb negatively influences folliculogenesis, spermatogenesis, fertilization rates, embryo quality and pregnancy rates.^[71]^ In Chinese women, idiopathic low ovarian reserve is associated with more frequent positive TPOAb.^[32]^ Therefore, TPOAb and TGAb will be used as the primary outcome to assess the effect of acupuncture on delaying or preventing disease progression and improving fertility in child-bearing period female with HT. Except for thyroid antibodies, evaluation of thyroid function in patients with HT is carried out by measuring the serum levels of thyrotropin (TSH), free thyroxine (FT4), free triiodothyronine (FT3).^[7]^ Anti-Mullerian hormone (AMH) is secreted by the granulosa cells of growing ovarian follicles.^[72]^ AMH is a suitable biomarker of ovarian age in women of reproductive age and the most widely used and reliable serum biomarker of ovarian reserve.^[61,73]^ Follicle stimulating hormone (FSH) stimulates growth of ovarian follicles and aromatase expression in follicle granulosa cells. During reproductive aging in females, a rise in basal FSH is considered a sign of the reduction in the follicle reserve.^[74]^ Basal estradiol level is usually lower than 50pg/mL. It can indicate reproductive aging and hastened oocyte development if greater than 60 to 80 pg/mL in the early follicular phase.^[75]^ Luteinizing hormone (LH) plays an essential physiological role in follicle steroidogenesis and development and oocyte maturation. High basal LH levels are associated with significantly reduced fertilization rates and oocyte maturation, as well as impaired embryo quality, consequently resulting in an impaired pregnancy rate and higher miscarriage rate.^[76,77]^ Collectively, ovarian function will be assessed using the basal endocrine in the early follicular phase.

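### The primary outcome is defined in two incompatible ways, with no rule for combining TPOAb and TGAb; whichever rule is meant, the stated 5% error or the stated 80% power does not hold

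*Protocol article*

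**What the plan says.** The protocol article defines the primary outcome twice.

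- **Section 6.1, Primary outcome:** "The primary outcome in this trial is the titers of TPOAb and TGAb at baseline and at the 4th, 8th, and 12th week". This covers two antibodies at three post-baseline visits.
- **Section 2.6, Sample size:** "The primary outcome of this study will be the mean change of TPOAb and TGAb from baseline to week 12". This covers two antibodies at one time point, as a change score.

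On how the two antibodies combine, section 2.1 (Design) says the trial is to "determine if acupuncture has an effect on the reduction of antibody (TPOAb or TGAb) and fertility improving". The Abstract, section 2.6, section 6.1 and the Discussion all join the two with *and*. None of them states a success rule.

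On the error rate, section 6.5 (Statistical analysis) says "All the tests will be two-sided", and a P "value of less than .05 will be considered statistically significant". It gives no ordering, no adjustment and no requirement that both antibodies succeed. It also names a repeated-measures analysis for each variable over the four testing times.

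On size, section 2.6 takes pilot TPOAb titers of 253.86 (SD 178.23) and 318.98 (SD 201.37) IU/ml and arrives at 134 per group at two-sided 0.05 and 80% power. The article gives no TGAb mean, difference or SD.

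**The concern.** A reader cannot tell from the article which result would count as primary success. The two definitions differ in the time points (week 12 or all visits) and in the measure (change or titer). Neither says what follows if one antibody responds and the other does not.

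The stated 5% and 80% both belong to a trial with one primary test, on TPOAb. With two primary variables, the 5% does not hold if either may succeed, and the 80% does not hold if both must. The missing rule therefore decides which of the two stated figures is wrong. It also leaves the choice open until the results are known.

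**Working it through.** **1. The plan's own figure.** Inputs from section 2.6:

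- difference: 318.98 − 253.86 = 65.12 IU/ml
- pooled SD: √((178.23² + 201.37²)/2) = 190.15
- standardised difference: 65.12/190.15 = 0.342
- n per group = (178.23² + 201.37²)(1.960 + 0.842)²/65.12² = 133.85, rounded up to 134

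The stated 134 reproduces. It uses TPOAb only and an undivided 0.05.

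**2. If either antibody suffices (two tests).** The false-positive rate is 1 − P(|Z₁| ≤ 1.96 and |Z₂| ≤ 1.96). If independent, this is 1 − 0.95² = 0.0975. The article gives no correlation between the two test statistics, so a range is assumed (bivariate normal):

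| Correlation | False-positive rate |
|---|---|
| 0 | 9.75% |
| 0.3 | 9.5% |
| 0.5 | 9.1% |
| 0.7 | 8.3% |
| 0.9 | 7.0% |

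**3. If each visit were also a primary test (six tests).** With independence, 1 − 0.95⁶ = 0.265. Serial titers in the same women are correlated, so this is a ceiling. Simulation (400,000 draws) gives about 14% to 23% for an assumed correlation of 0.5 to 0.9 over time and 0 to 0.7 between antibodies, and 11.5% when both are 0.9.

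**4. If both antibodies must succeed.** The error rate stays at or below 5%. For power, assume TGAb has the same standardised effect as TPOAb, 0.342. At 134 per group:

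- noncentrality per test: 0.342 × √(134/2) = 2.80
- power per test: Φ(2.80 − 1.96) = 0.80
- joint power: 0.80² = 64% if independent, 69% at correlation 0.5, 75% at 0.9

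With all 142 per group analysed, power per test is 82%, so joint power is 0.823² = 68% if independent. By the same bivariate normal calculation it is 72% at correlation 0.5 and 78% at 0.9.

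**5. If alpha were split instead (0.025 each).** With the TPOAb inputs kept, n is 163 per group, or 163/0.9 = 182 per group (364 in total) with 10% dropout. Power at 0.025 is 71% with 134 per group and 74% with 142.

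**6. TGAb in particular (illustration only).** The Discussion gives "TGAb (positive in only 60%–80% of HT patients", and the inclusion criteria do not require TGAb positivity. Suppose that 60% to 80% of enrolled women are positive, with an effect of 0.342 in positives and none in negatives. At 142 per group, TGAb power is then about 41% to 64% if the SD is unchanged. It is about 61% to 73% if negatives add no variance, so that the SD shrinks by the square root of the positive fraction.

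**The case against.** The strongest case on the other side has four parts.

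- **The either-or rule is an inference.** The only *or* stands in the general aim in section 2.1, and every other section says *and*. A reader might infer that success on either antibody is the planned criterion. The article does not say so, and if both are required the 5% holds. This stands. It turns the problem into one of power rather than removing it.
- **Six primary tests are not planned.** A reader might take section 6.1 as six separate primary comparisons and quote a 26% error rate. The article does not support that. Section 2.6 fixes week 12, section 6.5 names one repeated-measures analysis per variable, and section 6.1 lists baseline among its times, so it may be no more than a measurement schedule. The figure also needs independence, which serial titers lack. This stands: 26.5% is a ceiling on a reading that the wording permits but does not state.
- **The TGAb power figures are borrowed.** The article gives no TGAb effect or SD, and 60% to 80% describes HT patients in general, not the women enrolled here. It cannot be stated as fact that 20% to 40% of participants will have no raised TGAb. What is supported is that the sample size has no TGAb input.
- **Multiplicity is often left to the analysis plan.** The full protocol and any analysis plan are not shown, and a hierarchy may be set out there. This stands for the absence of an adjustment. It does not cover two definitions of the primary outcome in the same article: an analysis plan cannot follow both section 2.6 and section 6.1 as written.

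**Conclusion.** The concern holds in this form: two incompatible primary definitions, no rule for combining the antibodies, 0.05 for every test, and a sample size built on TPOAb alone.

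The consequence depends on the missing rule. If either antibody suffices, the primary false-positive rate is about 7% to 10% over assumed correlations of 0 to 0.9, and larger only if visits are also tested separately as primary. If both must succeed, the error rate is controlled but joint power at 134 per group is about 64% to 75%, on the assumption that TGAb shares TPOAb's standardised effect. Neither rule delivers both the stated 5% and the stated 80%.

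The documents do not support a flat statement that the error rate is 26%, or that the trial will declare success on any one comparison. The effect of TGAb-negative women on TGAb power is illustrative and carries no weight in this conclusion.

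**What to change.** - Name TPOAb at week 12, as change from baseline, as the single primary endpoint, tested at two-sided 0.05. This is the antibody on which the sample size rests.
- Test TGAb at week 12 next in a fixed sequence, at 0.05, only if TPOAb is significant. A supporting analysis in women TGAb positive at baseline may be added.
- Make weeks 4 and 8 secondary for both antibodies.
- Align the Abstract, section 2.1 (replacing the *or*), sections 2.6 and 6.1, and the Discussion with this definition, and state the order of testing in section 6.5.

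This keeps the 5% and the existing TPOAb power calculation, and needs no more patients on this account. Requiring both antibodies, or splitting alpha, would also settle the rule. The first costs power (step 4) and the second raises the number to 163 per group before dropout (step 5).

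The cost is more than an edit of wording. Section 2.1 says the trial is already being performed, and it is registered and ethics-approved, so the change needs a documented amendment, dated before unblinding, with the registry entry checked against it. The downside is that a result on TGAb alone, or at an earlier visit alone, can no longer be claimed as a primary success.

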### Secondary outcomes

6.2

The secondary outcomes include:

(1)thyroid function test including free triiodothyronine (fT3), free thyroxine (fT4), and thyroid stimulating hormone (TSH);(2)ovarian function including Anti Mullerian Hormone(AMH), follicle stimulating hormone (FSH), luteinizing hormone (LH), and estradiol (E2);(3)pregnancy outcome including pregnancy rate (%), pregnancy losses (%), and live birth rate (%);(4)primary ovarian insufficiency (%).

The thyroid function test will be performed at the baseline, 4th, 8th, and 12th week after randomization. The ovarian function will be examined on the 2nd to 4th day of the menstrual period in the 1st month, 2nd month and 3rd month compared with baseline (-1st month). Both the pregnancy outcome and the rate of primary ovarian insufficiency will be evaluated at 6 months and 1 year after treatment.

### Assessment of adverse events

6.3

Any adverse events, including acupoint hematoma, bleeding, fainting, serious pain, infection, stuck needles, and broken needles, will be recorded by the researcher. If adverse events occur during the intervention, management will be taken emergently. Serious adverse reactions will be reported to the ethical committee and rescue procedures will be initiated at once.

### Quality control and trial monitoring

6.4

Before the trial, all researchers involved will receive specialized training to maintain the study quality. The training courses include how to select and exclude patients, how to stratified randomization, how to manipulate interventions correctly, how to fill the case report form, how to assess outcomes and manage data. When the clinical trial begins, the principle researcher will supervise the trial. The licensed acupuncturists who have more than 5 years of experience will perform intervention according to the pre-specified standard operating procedure. Raw data will be recorded in the case record form (CRF). Two data managers enter the data into the spreadsheet and check the electronic data respectively. To guarantee the objectivity of the data, effect assessment and statistics will be blinded during the study period. Measures are taken to improve compliance, such as health education, respect patients informed consent right sufficiently etc.

### Statistical analysis

6.5

Statistical analyses of data will be performed using SPSS21.0 software (International Business Machines Corp., Armonk, NY) by professionals who will be blinded to the whole trial process. According to the principle of intention-to-treat (ITT), all randomized participants will be analyzed. Continuous variables with normal distribution will be expressed as Mean ± Standard Deviation (M ± SD) and compared by an independent sample Student *t* test. For abnormally distributed variables, they will be expressed as Medians ± Interquartile Range (MIQR) and nonparametric tests will be used. Categorical variables will be presented by frequency and percentage and analyzed by χ^2^ test or Fisher exact test. A repeated-measures multifactorial analysis will be used to analyze value changes of TPOAb, TGAb, fT3, fT4, TSH, thyroxine, AMH, FSH, LH, and E2 across 4 testing time points (See Table 1). The rest of the secondary outcomes will compare the proportions of patients with primary ovarian insufficiency and different pregnancy outcome. Safety analyses will be compared with the incidence of AEs in two groups using the χ^2^ test. Missing data will be handled by multiple imputation methods. All the tests will be two-sided, and a *P* value of less than .05 will be considered statistically significant.

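### The primary antibody comparison does not use baseline titre or TSH stratum as a covariate, and the plan does not say which of its two analyses decides

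*Protocol article*

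**What the plan says.** All places are in the protocol article.

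- **Statistical analysis (6.5), first method.** Normally distributed continuous variables are compared by an independent-samples t test. Otherwise: "For abnormally distributed variables, they will be expressed as Medians ± Interquartile Range (MIQR) and nonparametric tests will be used". The nonparametric test is not named.
- **Statistical analysis (6.5), second method.** "A repeated-measures multifactorial analysis will be used to analyze value changes of TPOAb, TGAb, fT3, fT4, TSH, thyroxine, AMH, FSH, LH, and E2". This second analysis runs "across 4 testing time points". The section does not say whether the group effect or the group-by-time effect is the one of interest, or how this analysis ranks against the first.
- **Primary outcome (6.1).** The titres of both antibodies at baseline and weeks 4, 8 and 12. These are the four times, so the pre-treatment value counts as one of the responses.
- **Sample size (2.6).** Here the primary outcome is the mean change from baseline to week 12. The calculation, however, uses titres by group: "titers of TPOAb was 253.86 ± 178.23 IU/ml in the acupuncture group and 318.98 ± 201.37IU/ml in the sham acupuncture group". It concludes that "at least 134 patients should be enrolled in each group" and that "284 total participants will be recruited to allow for a 10% dropout rate".
- **Randomization (2.7).** Allocation is stratified by TSH (below 2.5 versus 2.5 to below 5 mIU/L). The analysis section does not mention the stratum.

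**The concern.** Baseline titre is measured on everyone and is likely to predict the week-12 titre strongly. Entering it as a covariate removes the variance that it explains and corrects for chance imbalance. The plan does not do this, nor does it carry the stratification factor into the analysis.

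The plan also leaves the deciding result open in three ways: the test depends on the distribution seen, a second analysis of the same antibodies stands beside it, and that second analysis yields more than one P value. The two definitions of the primary outcome add to this.

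The switch to a rank test is a likely path. The pilot SDs are 70% and 63% of their means (178.23/253.86 and 201.37/318.98). Mean minus 2 SD is −102.6 and −83.8 IU/ml, for a quantity that cannot be negative, so skewed titres are to be expected. A rank test would not by itself estimate the mean change that the sample size section names.

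**Working it through.** **Inputs from the document.** Two-sided α 0.05 and 80% power; TPOAb 253.86 (SD 178.23) against 318.98 (SD 201.37) IU/ml; 1:1 allocation; 134 per group; 142 per group recruited; 10% dropout.

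**Assumed.** The correlation ρ between baseline and week-12 titre is not given. It is varied below, with equal variance at each time.

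**1. The plan's own figure.** Difference Δ = 318.98 − 253.86 = 65.12. Pooled SD σ = √[(178.23² + 201.37²)/2] = 190.15.

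n = 2 × 7.849 × 190.15² / 65.12² = 133.9, so 134 per group. This reproduces the stated number as an unadjusted comparison of follow-up titres.

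**2. Baseline as covariate, as change score, or not at all.** With 10% dropout, 142 × 0.9 = 127.8, so 128 per group. Power = Φ(Δ / (SD × √(2/n)) − 1.96), where SD is:

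- unadjusted week-12 titre: σ
- change score: σ√(2(1 − ρ))
- baseline-adjusted week-12 titre: σ√(1 − ρ²)

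| ρ (assumed) | Unadjusted titre | Change score (SD) | Baseline-adjusted (SD) |
|---|---|---|---|
| 0.3 | 78% | 64% (225.0) | 82% (181.4) |
| 0.5 | 78% | 78% (190.2) | 89% (164.7) |
| 0.7 | 78% | 94% (147.3) | 97% (135.8) |

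Worked line for ρ = 0.5, adjusted: 65.12 / (164.7 × √(2/128)) = 3.16, and Φ(3.16 − 1.96) = 0.886.

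**3. Baseline as one of four responses.** If the group main effect decided, the tested quantity would be the mean over four times, with SD σ√((1 + 3ρ)/4) under compound symmetry. The baseline contributes no treatment effect, so the mean effect is 0.75Δ if the full effect is present from week 4, and 0.5Δ if it grows linearly to week 12. At 134 per group:

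| ρ (assumed) | Full effect from week 4 | Linear growth |
|---|---|---|
| 0.5 | 76% | 43% |
| 0.7 | 67% | 36% |
| 0.9 | 59% | 31% |

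The group-by-time test is not diluted in this way. Simulated at 134 per group (3,000 runs, normal data), its power at ρ = 0.5, 0.7 and 0.8 is 83%, 97% and 99.8% with the full effect from week 4, and 70%, 91% and 98.5% with linear growth. The unadjusted week-12 t test has about 80%.

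**4. What the open choice could cost.** In the same simulations without any effect, taking the smallest P value of the t test, the group effect and the group-by-time effect gave a type I error of about 11% to 13% per antibody. This shows what is possible if the choice stays open. The plan does not say that the smallest P value will be taken.

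**The case against.** The strongest reply is that a condensed article may leave the covariate list, the transformation and the contrast within the model to a full analysis plan. That holds for detail. But the article itself fixes unadjusted tests, a distribution-dependent choice and a second analysis of the same outcome, and it gives two definitions of that outcome. A later plan would have to change this text, not merely fill it in.

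Four stronger readings are tempting, and the document does not support them.

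- *The plan ignores baseline.* It does not. The sample size section defines the outcome as change from baseline, and a group-by-time test uses baseline as a level. What is missing is baseline as a covariate. Against change scores at ρ = 0.7 the gain is about 3 points (94% to 97%), not the 19 points seen against unadjusted titres.
- *Counting baseline as a response must lose power.* This is true of the group main effect only, and the plan does not name that effect as decisive. The wording about changes in values over time fits the group-by-time test at least as well.
- *Skewed titres make the planned analysis weak.* If titres are log-normal with the pilot means and SDs, simulated power at 128 per group is 92% for the rank test and 93% for a t test on log titres. The planned switch recovers nearly all of the gain. Nor does a switch triggered by a normality test inflate type I error noticeably: 4.8% to 5.5% in simulation at 134 per group. Its harm is to clarity and to what is being estimated, and a Hodges-Lehmann shift could accompany the rank test.
- *There are three rival primary results.* The t test and the rank test are alternatives. Each antibody gets two analyses, one of which yields several P values.

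**Conclusion.** The point holds as a low-cost improvement that should be made. The primary comparison uses neither baseline titre nor TSH stratum as a covariate, the deciding analysis and effect are not named, and the sample size and primary outcome sections disagree on the endpoint.

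The benefit of baseline adjustment depends on a correlation that the document does not give. Over 0.3 to 0.7 it adds about 4 to 19 points of power over unadjusted titres, and about 18, 10 and 3 points over change scores at 0.3, 0.5 and 0.7. These figures rest on the pilot TPOAb difference and SDs, approximate normality and 128 per group. No pilot figures are given for TGAb, so its gain cannot be sized.

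The low main-effect powers (76% to 59%, or 43% to 31%) are conditional: they apply only if that effect were declared decisive.

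**What to change.** Name one primary analysis for each antibody, and align the sample size and primary outcome sections with it:

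- **Contrast:** acupuncture versus sham at week 12, in log titre.
- **Model:** ANCOVA at week 12, or a linear mixed model with weeks 4, 8 and 12 as responses. Baseline is a covariate and not a response.
- **Covariates:** log baseline titre and the TSH randomisation stratum.
- **Report:** geometric mean ratio with 95% CI.
- **Sensitivity analysis:** the rank test, named in advance, in place of a switch that depends on the observed distribution.

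This should be fixed before unblinding. It costs a paragraph of text and a little programming in the software already planned, with no extra data or patients. The downside is that the effect is reported as a ratio rather than in IU/ml.

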### Randomization

2.7

As the cutoff value of LT4 supplementation based on TSH level is controversial in women who are trying to conceive, the participants will be stratified by TSH level (TSH < 2.5 mIU/L vs 2.5 mIU/L≤TSH < 5 mIU/L). Once consent has been obtained and baseline data collected, participants will be randomized to the acupuncture group (n = 142) or the the sham acupuncture group (n = 142). Randomization will be performed according to a random list of numbers generated with SPSS21.0 software (International Business Machines Corp., Armonk, NY). An independent researcher will prepare the assignments in opaque envelopes containing an allocation sequence number and take charge of the allocation sequence concealment.

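### Safety is tested with chi-square alone against a sham needle that is not inserted; the sparse tables that result call for counts with exact intervals rather than a P value

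*Protocol article*

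**What the plan says.** - **Safety analysis (section 6.5, Statistical analysis).** The plan states "Safety analyses will be compared with the incidence of AEs in two groups", and the only method this sentence names is the χ² test.
- **Significance rule (same section).** "All the tests will be two-sided, and a *P* value of less than .05 will be considered statistically significant". No exception is made for safety.
- **General rule for categorical data (same section).** "Categorical variables will be presented by frequency and percentage and analyzed by" a χ² "test or Fisher exact test". The general rule therefore offers an exact test that the safety sentence does not repeat.
- **Events recorded (section 6.3).** "Any adverse events, including acupoint hematoma, bleeding, fainting, serious pain, infection, stuck needles, and broken needles" are to be recorded. The seven named events are examples, not a closed list. Serious reactions go to the ethics committee regardless of any test.
- **Comparator (section 5, Sham acupuncture group).** The device has a blunt tip and is "similar to Streitberger needles device, without insertion". In the acupuncture group (section 4) the needles are inserted at all eight points.
- **Numbers (section 2.7, Randomization).** 142 women per arm.

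**The concern.** Most of the events named in section 6.3 are complications of a needle passing through skin. Against a needle that is not inserted, their count in the sham arm should be at or near zero because of the design. For those events the useful question is how often they occur with real needling and how precisely the trial can say so. A chi-square P value answers neither part. It is also least dependable in sparse tables, which are the tables to expect here, and the sentence names it without the exact alternative that the general rule provides.

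What is at stake is the informativeness of the safety report. A handful of needle-related events in one arm and none in the other could appear as a P value above .05 with nothing beside it to show how high the underlying risk might be.

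**Working it through.** The document gives no figure for the safety comparison, so there is none to reproduce. The check asks what the named test does with small counts.

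**Inputs.** n = 142 per arm (section 2.7); two-sided α = .05 (section 6.5); no insertion in the sham arm (section 5). *Assumption:* an event type is tested on its own, k women in the acupuncture arm have it, and none in the sham arm do.

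**Step 1: expected counts.** With equal arms, the expected count of women with the event is half the total in each arm. It is below 5 whenever fewer than 10 women in all have the event. For k = 1 to 6 against 0 it runs from 0.5 to 3.

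**Step 2: P values.**
- Uncorrected Pearson chi-square for k/n against 0/n reduces to 2nk/(2n − k).
  - k = 3: 284 × 3 / 281 = 3.03
  - k = 4: 284 × 4 / 280 = 4.06
- Fisher two-sided is 2 × C(142, k) / C(284, k).
  - k = 4: 2 × (142 × 141 × 140 × 139) / (284 × 283 × 282 × 281) = 0.122

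**Step 3: exact (Clopper-Pearson) 95% CI for k/142.**

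| Events, acupuncture v sham | Pearson P | Fisher P | Acupuncture-arm risk (exact 95% CI) |
|---|---|---|---|
| 0 v 0 | not defined | not informative | 0% (upper limit 2.6%) |
| 1 v 0 | 0.32 | 1.00 | 0.7% (0.02% to 3.9%) |
| 2 v 0 | 0.16 | 0.50 | 1.4% (0.2% to 5.0%) |
| 3 v 0 | 0.082 | 0.25 | 2.1% (0.4% to 6.0%) |
| 4 v 0 | 0.044 | 0.12 | 2.8% (0.8% to 7.1%) |
| 5 v 0 | 0.024 | 0.060 | 3.5% (1.2% to 8.0%) |
| 6 v 0 | 0.013 | 0.030 | 4.2% (1.6% to 9.0%) |

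The P = .05 line falls between 3 and 4 events by Pearson and between 5 and 6 by Fisher. With Yates' correction it also falls between 5 and 6 (0.071 and 0.039). With 134 or 128 women per arm the line falls in the same places. The interval is the same whichever test is chosen.

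**Step 4: how often the test would stay above .05.** The document gives no event risk, so a range is assumed for the risk per woman in the acupuncture arm, with none in the sham arm.

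| Assumed risk | P(at most 3 events): Pearson not significant | P(at most 5 events): Fisher not significant |
|---|---|---|
| 1% | 94% | 99.7% |
| 2% | 68% | 93% |
| 3% | 38% | 75% |
| 5% | 7% | 28% |

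**Step 5: if all adverse events are tested together.** Events common to both arms raise the bar. With 2, 5 or 10 background events per arm, the smallest excess in the acupuncture arm that reaches P < .05 by Pearson is 7, 9 or 11.

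**The case against.** The other side has a good deal to say.

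- **Counts and percentages are already planned.** The general rule for categorical variables supplies them, and adverse event occurrence is categorical, so a reader would see 3/142 beside 0/142. Serious reactions are escalated independently. This stands: safety does not rest on the P value alone.
- **One-arm-only harms.** A reader might infer that five of the seven named events cannot occur under sham. The documents do not say so. The blunt needle touches the skin and is mock-manipulated at each point, so a bruise or a device fault is conceivable, and the list is only illustrative. At or near zero is as far as the text supports.
- **A threshold of three.** A reader might infer that up to three needle harms would always be non-significant and four would not. That holds only for puncture events tested alone by uncorrected Pearson with none under sham. The safety sentence does not say whether it means any event or each type.
- **False reassurance.** A reader might infer that P > .05 will be reported as proof of safety. Nothing in the protocol says this, and no safety hypothesis or margin is set.
- **Wrong unit.** A reader might fear that events or sessions will be counted as independent. Nothing proposes that.
- **Chi-square is not invalid here.** Its type I error is not inflated: 0.6% to 4.8% for common true rates of 0.5% to 5%. Fisher alone would make more low counts non-significant.
- **Detail may sit elsewhere.** Tables by event type and intervals are often left to a full protocol or analysis plan. That is fair for what is merely absent, but the published sentence does specify a test, and more narrowly than the article's own general rule.

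**Conclusion.** The point holds in a limited form. The safety sentence fixes a single test that suits the expected tables poorly and omits the exact alternative allowed in the same section. Because the sham needle is not inserted, a P value on puncture-dependent events carries little information about harm, and near the .05 line it depends on the test chosen (4 v 0 gives 0.044 or 0.12). An exact interval on the same data bounds the risk directly: 0.4% to 6.0% for 3 of 142, and at most 2.6% for none.

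The figures assume 142 women analysed per arm, each event type tested separately, and no such events under sham. The risks of 1% to 5% in the working are illustrative. The comparison with sham is still worthwhile, above all for fainting and pain, which can occur in either arm. The primary conclusion is not affected. This is a minor, cheap improvement.

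**What to change.** Amend the safety sentence in section 6.5 so that it:

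1. reports, for any adverse event and for each type, by arm, the number and percentage of women with at least one event, with an exact 95% CI;
2. gives the between-arm risk difference with its 95% CI;
3. uses Fisher's exact test where expected counts are below 5, in line with the general rule in the same section;
4. states that P > .05 will not be read as evidence of safety.

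**Cost.** A few sentences and a larger safety table, with no extra data or patients. Fisher will bring fewer low counts below .05, so the intervals rather than the P value should carry the safety conclusion.
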